#### Cardiometabolic risks and mortality

The descriptive analysis of primary and secondary outcomes will provide useful summaries about the sample and the outcome measures. Besides the unadjusted descriptive statistics, such as the incidence rate of each outcome, simple graphics analysis will be provided.

Causal inference in the analysis of cardiometabolic outcomes and mortality will be undertaken using inverse propensity weighting (IPW). This method was empirically shown to be superior to other propensity score-based approaches in analysis of multiple treatments with a binary outcome.^27^ The propensity-score matching, even though well valuated in two-arm treatment, in multiple treatments might introduce bias; the IPW is more efficient in such scenario. Additionally, IPW method is more flexible and requires weaker unconfoundedness assumption.^28^

Generalised propensity weights with treatment category as dependent variable will be calculated in the multinominal logistic model.^29^ The model will be developed using the following covariates: age at the index date, sex, baseline serum fT4, aetiology of hyperthyroidism, smoking status, IMD, cumulative time on ATD between diagnosis and the index date, time since diagnosis and BMI status.

Variables related to treatment, as an outcome, at p<0.10 will be selected for inclusion in the multiple propensity weights.^30^ To identify these variables, we will conduct several regression analyses with the treatment as a dependent and each potential confounder as an independent variable. Furthermore, it will be investigated whether adding interaction terms or higher-order terms for continuous variables will improve the balance of the model. The Hausman test will be used to check the independence of irrelevant alternatives assumption, which is the main assumption of multinomial regression analysis.^30^ If this assumption is not met, multinomial probit analysis will be used instead.

The estimation of propensity weights will be conducted by the method proposed by McCaffrey *et al*.^31 32^ The appropriateness of IPW analysis will be assessed by checking the overlap (positivity assumption). According to the positivity assumption, each patient should have a non-zero probability of being indicated to each treatment category. Lack of overlap in the distribution of observed pretreatment characteristics between groups receiving different treatment indicates the positivity assumption is violated. This overlap will be checked visually. If poor overlap is identified, we will use Rubin’s trimming method,^33^ allowing discarding non-overlapping cases.

Further, pairwise balance in the distribution of all included variables between the three treatment groups will be tested with linear regression for continuous variables, logistic regression for binary and multinomial logistic regression for nominal variables. The analysis will be done without and with adjustments. The propensity weights will be considered balanced if there are no statistically significant (p<0.05) differences between the likelihood of receiving a different type of treatment. If imbalances remain after weighting, a doubly robust estimation approach will be applied^32^; that is, the imbalanced variables will be added to the model.

While IPW will adjust for confounding at baseline, other time-varying adjustments will be applied to correct for the events between the baseline and the outcome. The proposed covariates are treatment with levothyroxine for developed hypothyroidism, log TSH levels and informative observations of number of GP visits in a unit of time.

Incidence rate ratios of outcomes will be calculated with Poisson regression and modelled adjusting for time-varying covariates as listed further. Time-to-event analysis with adjustments will be modelled. The appropriate model will be applied, depending on the proportional hazard assumption’s results: if the assumption holds—Cox proportional hazard regression will be used; if it is violated, alternative techniques such as time-varying measures in extended Cox models will be applied.

Proposed time-varying adjustments for both analyses will include postindex date data, that is, treatment with levothyroxine for developed hypothyroidism, logTSH levels and informative observations of number of GP visits in a unit of time. To allow for the fact that patients may die, a competing risks approach will be adopted for estimating comparative incidences for non-fatal events to allow for the impact of mortality as a competing risk.^22^

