### Population

Adult patients (≥18 years) who were for the first time diagnosed with hyperthyroidism (the list of codes in online supplemental appendix) between 1 January 1996 and 31 December 2015 will be eligible for inclusion. To minimise missed cases, the diagnosis will be additionally identified by a prescription of carbimazole or propylthiouracil, which are ATDs indicated only for treatment of hyperthyroidism. A minimum of 12 months of data must be available before the date of diagnosis and after the index date. CPRD records need to be classified as acceptable research quality.

10.1136/bmjopen-2021-055219.supp1Supplementary data

Exclusion criteria encompass ATD treatment of duration shorter than 6 months as the only treatment, that is, with no radioactive iodine or thyroidectomy followed. This is to avoid contamination by misdiagnosis or spontaneously resolving thyroiditis. Patients treated with both definitive treatment methods, that is, radioiodine and thyroidectomy, will also be excluded. However, ATD treatment followed by either radioiodine or thyroidectomy (one of the definitive treatments) is considered a pretreatment and does not constitute an exclusion criterion.

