### Exposure

The exposure in the study is the treatment for hyperthyroidism. The study patients will be divided into three groups based on the treatment administered: (1) radioiodine: the allocation to this treatment arm will be assigned based on the Read code or OPCS-4 code of the treatment procedure for radioiodine; (2) thyroidectomy: the allocation to this treatment arm will be assigned based on the Read code or OPCS-4 code of the surgical procedure; (3) medical treatment arm will be identified based on the absence of radioiodine treatment code and thyroidectomy code in the presence of ATD treatment (based on the Read code or British National Formulary (BNF) code) longer than 6 months.

We anticipate good quality of ATD prescription and thyroidectomy. However, radioiodine, typically administered in outpatients, may be missed in a substantially high proportion of patients. Since ATD treatment does not incur permanent hypothyroidism, the long-term prescription of levothyroxine for hypothyroidism following treatment with ATD alone, that is, without any definitive procedures, will be considered as a proxy for radioiodine administration.

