### Index date and follow-up

The index date in the cohort is the date of initiation of treatment for hyperthyroidism, which defines the treatment group (either ATD, radioiodine or thyroidectomy). There is a requirement of at least 12 months’ data available prior to the index date.

The natural history of weight changes will be modelled preindex and postindex date. While the follow-up for the analysis of outcomes will start at the index date, a minimum of 12-month follow-up is required for the inclusion.

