#### Prevalence of obesity

Post-treatment obesity in patients will be defined as ≥30 kg/m^2^, in line with the WHO definition,^26^ or identified from the Read codes when quantitative values are not available. The prevalence of obesity will be assessed in the entire cohort and stratified by the treatment group.

The post-treatment BMI will be compared with those in the background population (Health Survey for England). Two measures of effect will be investigated: (1) difference in overall BMI (kg/m^2^) and (2) difference in proportions of obesity. The effects will be tested with linear regression and logistic regression, respectively, in reference to the background population. The analyses will be adjusted for age and stratified by sex. Only complete case analysis will be conducted.

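### Calendar year appears in no listed adjustment although diagnoses span 20 years, so secular trends may confound the treatment comparison; direction and size are unknown

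*Protocol article*

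**What the plan says.** The Population section admits adults first diagnosed "between 1 January 1996 and 31 December 2015 will be eligible for inclusion". Of the propensity model, the Cardiometabolic risks and mortality section says "The model will be developed using the following covariates", and lists them in two runs: "age at the index date, sex, baseline serum fT4, aetiology of hyperthyroidism, smoking status, IMD", then "cumulative time on ATD between diagnosis and the index date, time since diagnosis and BMI status". That makes nine variables, none of them calendar year. The Confounding section and Table 2 do not list it, and the time-varying adjustments are levothyroxine, log TSH and frequency of GP visits.

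Three design rules bear on how calendar time relates to treatment group:

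- Index date and follow-up: "The index date in the cohort is the date of initiation of treatment for hyperthyroidism, which defines the treatment group".
- Population: "ATD treatment followed by either radioiodine or thyroidectomy (one of the definitive treatments) is considered a pretreatment".
- Exposure: the "medical treatment arm will be identified based on the absence of radioiodine treatment code and thyroidectomy code", together with more than 6 months of antithyroid drugs (ATD).

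For obesity against the Health Survey for England, the Prevalence of obesity section says: "The analyses will be adjusted for age and stratified by sex". The Data sources section describes that survey as yearly and as tracking trends. Survey year is not mentioned as a matching or adjustment variable.

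**The concern.** Over 20 years, cardiovascular event rates, mortality, completeness of coding and the choice between drugs, radioiodine and surgery may all change. If they do, calendar time is related to both treatment group and outcome, and weights built without it need not balance it. Part of a rate ratio or hazard ratio for MACE, heart failure or death could then reflect when patients were treated rather than how. The section presents this analysis as causal inference, and in a large cohort a shift of a few percent can look precise.

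The obesity comparison has a smaller version of the same gap. Post-treatment BMI values will be spread over many calendar years, and a difference from the general population depends on which survey years they are set against.

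**Working it through.** **1. Would any planned step pick up calendar year?**

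- The p<0.10 screen tests candidate confounders against treatment. Calendar year is never named as a candidate.
- Balance is tested for the variables included in the weights, so an omitted variable is not tested.
- The doubly robust fallback adds only variables found imbalanced at that step.

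As written, an imbalance in calendar year would be neither seen nor corrected.

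**2. Do the listed variables replace it?** Index date = diagnosis date + time since diagnosis. Balancing time since diagnosis deals nominally with the lag, but leaves any difference in diagnosis year between arms. Age at index does not help: a patient aged 50 may be indexed in 1997 or in 2015.

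**3. How large could the gap between arms be?** The article has no figure to reproduce, so every input except the diagnosis window is an assumption.

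*(a) Constant treatment mix.* I simulated diagnosis dates uniform over 1996–2015, 30–50% destined for definitive treatment, exponential delay with mean 1–3 years, 0–30% treated without delay, and 12 months of follow-up after index. Data were assumed to end at the start of 2017 or of 2021. Gaps are definitive minus ATD, in years:

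| Data end | Mean index year | Mean diagnosis year |
|---|---|---|
| 2017 | +0.22 to +0.93 | −0.38 to −1.92 |
| 2021 | +0.66 to +2.34 | 0.00 to −0.48 |

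The diagnosis-year gap is negative because patients diagnosed late have less time to acquire a definitive code and so stay in the ATD arm.

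*(b) Changing mix.* Let the definitive share rise linearly from 30% to 50% over the window. Mean diagnosis time, in years from the start of 1996, is:

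- definitive: 20 × (0.30/2 + 0.20/3)/0.40 = 10.83
- ATD: 20 × (0.70/2 − 0.20/3)/0.60 = 9.44

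The gap is 1.39 years. With an assumed lag of 1.5 years, the index gap is 1.39 + 1.5 = 2.89 years. If the share falls from 50% to 30%, the diagnosis gap is −1.39 and the index gap is −1.39 + 1.5 = 0.11 years.

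**4. Effect on a null rate ratio.** For an assumed annual fall d in event rate and a gap g, the spurious ratio, definitive against ATD, is (1 − d)^g before any covariate adjustment:

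| Gap g (years) | d = 1% | d = 3% | d = 5% |
|---|---|---|---|
| +0.11 (falling share, with lag) | 0.999 | 0.997 | 0.994 |
| +0.93 (lag only, data to 2017, largest) | 0.991 | 0.972 | 0.953 |
| +2.34 (lag only, data to 2021, largest) | 0.977 | 0.931 | 0.887 |
| +2.89 (rising share, with lag) | 0.971 | 0.916 | 0.862 |
| −1.39 (falling share, lag balanced) | 1.014 | 1.043 | 1.074 |
| −1.92 (diagnosis year only, data to 2017, largest) | 1.019 | 1.060 | 1.103 |

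The shift runs from almost nothing to about 14% (1 − 0.862). Its sign depends on which part of the gap remains after weighting. If recorded event rates rise instead, for example through better coding, every sign reverses.

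**The case against.** The strongest reply is that the lag between diagnosis and definitive treatment is already in the model, through time since diagnosis and pre-index ATD time. That stands nominally. Time since diagnosis will be near zero in the ATD arm, so overlap may be poor, but that is a positivity question and the article plans overlap checks and trimming for it. What no listed variable covers is a difference in diagnosis year.

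A second reply is that the list may not be final. The Confounding section promises to explore potential confounders in the data and names comorbidities, which the propensity list lacks. The causal diagram and the full approved protocol are not shown. Either could include calendar year. Still, the article states its covariates explicitly, and none of its lists has it.

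A third reply is that the obesity comparison is a separate matter and that the choice of survey years may sit in the fuller protocol. That is fair and keeps this part small, but the adjustment the article does state covers age and sex only.

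A reader might infer more: that index dates fall later in the definitive arms by construction, so results must favour those arms. The documents do not support this. The later date follows only relative to a patient's own diagnosis and only for pretreated patients, and pretreatment is allowed, not required. The gap between arms depends on treatment mix over time and the end of data, neither of which is given. Nor is there support for gaps of 4 to 6 years, which would give 0.97^4 = 0.885 or 0.96^6 = 0.783; the largest gap found under the assumptions above is 2.89 years.

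**Conclusion.** The point holds as a risk of residual confounding. Calendar year is absent from every printed adjustment list of a cohort diagnosed over 20 years, the listed variables do not replace it, and the planned checks would not reveal the omission. The documents do not show that a bias exists, which arm it would favour or how large it would be. On assumed gaps of about 0 to 3 years and trends of 1 to 5% a year, the null rate ratio moves by roughly 0 to 14% before adjustment, in either direction. The obesity comparison shares the gap in smaller form; no size can be given for it. The change is worth making because it is cheap and the analysis is meant to be causal.

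**What to change.** Add calendar year of index or diagnosis to the propensity model, as a spline or in period bands, and retain it whatever the p<0.10 screen shows. Include it in the pairwise balance checks and report its distribution by arm before and after weighting. In the obesity comparison, match or adjust survey year to the year of each post-treatment BMI.

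The dates needed are already used to define the cohort, so no new data are required for the treatment comparison. The downside is slightly more variable weights if an arm is rare in some years; period bands limit this.

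### Time zero is ATD start in one arm and the later procedure in the others, so positivity fails for every ATD-pretreated procedure patient and mortality is biased in favour of the procedures

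*Protocol article*

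**What the plan says.** Under Index date and follow-up: "The index date in the cohort is the date of initiation of treatment for hyperthyroidism, which defines the treatment group". The same section adds that "the follow-up for the analysis of outcomes will start at the index date" and requires at least 12 months of follow-up.

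Under Population: "ATD treatment followed by either radioiodine or thyroidectomy (one of the definitive treatments) is considered a pretreatment". Such patients stay eligible and belong to the procedure arm.

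Under Exposure, the "medical treatment arm will be identified based on the absence of radioiodine treatment code and thyroidectomy code in the presence of ATD treatment" for longer than 6 months. No time limit is put on the absence of a procedure code.

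Table 2 defines pretreatment ATD as the time accumulated on ATD from diagnosis to index, and baseline fT4 as the highest value from 3 months before diagnosis up to index.

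Under Cardiometabolic risks and mortality, the covariates for the multinomial propensity model end with "cumulative time on ATD between diagnosis and the index date, time since diagnosis and BMI status", subject to a p<0.10 screen for association with treatment. The section then states: "According to the positivity assumption, each patient should have a non-zero probability of being indicated to each treatment category". Overlap is checked visually. Poor overlap leads to trimming, and residual imbalance leads to adding the imbalanced variables to the outcome model.

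**The concern.** Read together, these definitions start the clock at different stages of disease in different arms. There are two separate consequences.

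First, a covariate that is fixed at zero in one arm by definition is used to predict membership of that arm. The weighted comparison of ATD with the procedures then has no support among patients who took ATD before their procedure.

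Second, membership of the ATD arm depends on what happens after its index date. A patient who survives on ATD long enough to have a procedure moves, with all earlier time, out of the ATD arm. A patient who dies first stays in it.

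At stake are the treatment comparisons of mortality and cardiometabolic outcomes, which the protocol presents as causal inference intended to inform treatment choice.

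**Working it through.** The protocol gives no figure to reproduce here. The overlap result follows from its definitions alone; the size of the mortality bias needs assumptions, which are stated below.

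**Overlap.** Let A be cumulative ATD time from diagnosis to index.

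- ATD arm: index is ATD start, so A = 0 for everyone.
- Procedure after ATD: index is the procedure, so A > 0.
- Procedure without earlier ATD: A = 0.

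Hence P(ATD arm | A > 0) = 0 exactly, at any sample size. Overlap with the ATD arm is possible only at A = 0, with first-line procedure patients.

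The share f of procedure patients treated first-line is not given. Assume 60% of the cohort is in the ATD arm and 40% had a procedure. At A = 0, P(ATD) = 0.6/(0.6 + 0.4f), and a first-line procedure patient's weight is 1/(1 − P(ATD)).

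| f | Procedure patients with no ATD counterpart | P(ATD given A = 0) | Weight of first-line procedure patient |
|---|---|---|---|
| 0% | 100% | 1 | none exist |
| 10% | 90% | 0.6/0.64 = 0.94 | 16 |
| 30% | 70% | 0.6/0.72 = 0.83 | 6 |
| 50% | 50% | 0.6/0.80 = 0.75 | 4 |

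Trimming would remove the patients in the second column. Adding A to the outcome model instead does not help: A does not vary in the ATD arm, so the adjusted contrast at A > 0 is extrapolated.

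**Related covariates.** Time since diagnosis at index will be short in the ATD arm and longer after pretreatment. It is exactly zero only where the prescription itself identifies the diagnosis, so this is a softer problem. Baseline fT4 is a maximum over a window that is longer in pretreated patients; extending the window can only leave the maximum unchanged or raise it.

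**Mortality follow-up.** Let q be the share of all ATD person-time that belongs to later switchers. With an equal constant death hazard λ in all arms, the correct ATD rate is λ. The protocol's grouping keeps the ATD deaths but drops q of the person-time, giving λ/(1 − q). Without the 12-month rule the null rate ratio, procedure to ATD, is therefore 1 − q.

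Hand check: if 40% switch at 1.5 years and the other 60% contribute 8 years each, q = 0.4 × 1.5/(0.6 × 8 + 0.4 × 1.5) = 0.6/5.4 = 0.111, and the ratio is 0.89.

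A null simulation used 2,000,000 patients per scenario. Assumed inputs: death hazards of 0.01, 0.02 and 0.04 per year, 10% first-line procedures and a 10-year horizon. Ranges are over the three hazards.

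| Assumed switching | q | Ratio without 12-month rule | Ratio with rule | Time-updated exposure |
|---|---|---|---|---|
| 0.1 per year for 5 years | 13–14% | 0.86–0.87 | 0.88–0.89 | 1.00 |
| 0.2 per year for 5 years | 27–28% | 0.72–0.73 | 0.78–0.79 | 1.00 |
| 0.3 per year for 3 years | 16–17% | 0.83–0.84 | 0.91–0.92 | 1.00 |

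The true ratio is 1.00 throughout. The third column agrees with 1 − q. The fourth is the one that applies to this protocol.

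**Non-fatal outcomes.** For a non-fatal event at the same hazards, with switching independent of the event and no deaths, the protocol's grouping gives 0.99 to 1.00. The event does not prevent a later procedure, so events and person-time leave the ATD arm together.

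**The case against.** Several stronger readings are tempting, and the protocol does not support them.

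- *The propensity model has no overlap at all.* Not so: a procedure without prior ATD is allowed, and those patients can overlap with the ATD arm at zero.
- *The weights are undefined.* Each patient is weighted by the inverse probability of the treatment received, so weights stay finite even when a coefficient diverges. The defect is that nobody in the ATD arm can represent the pretreated stratum.
- *All early deaths count against ATD.* The 12-month follow-up requirement and the minimum of 6 months on ATD exclude early deaths. The rule reduces the bias without removing it.
- *Every event rate in the ATD arm is inflated.* The mechanism needs an event that prevents later switching. It covers all-cause and cardiovascular mortality and the fatal part of MACE. It does not cover diabetes or other outcomes in so far as they are non-fatal and do not alter switching.
- *Switchers' ATD time is discarded from the study.* It is lost only from outcome follow-up. It remains as a covariate, and the weight analysis keeps it, because the treatment phase there starts at diagnosis, first dose or procedure.

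One may also read the index date as the first treatment of any kind for everyone. Pre-index ATD time would then be zero in all arms and serve no purpose as a covariate, and time on ATD before a procedure would become immortal time credited to the procedure. That reading exchanges one bias for another.

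Finally, the protocol does plan an overlap check and a remedy. That is fair, but the remedy changes the question being answered and leaves the mortality bias in place.

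**Conclusion.** The point stands in two parts, both limited to the secondary cardiometabolic and mortality analyses.

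1. Positivity as the protocol defines it fails structurally for every pretreated radioiodine or thyroidectomy patient. This needs no outside data. How much of the procedure arms is affected depends on the first-line share, which is not stated.
2. The grouping favours the procedures on all-cause mortality, cardiovascular mortality and the fatal part of MACE. The null rate ratio is about 0.78 to 0.92 with the 12-month rule. The direction was the same in every scenario; the size rests on the assumed hazards, switching rates, first-line share and horizon.

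This should be corrected before analysis, because the index date, arm definitions and covariate list as stated cannot satisfy the stated weighting assumption.

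**What to change.** For the cardiometabolic and mortality analyses, set time zero at first treatment (or diagnosis) for all patients. Treat exposure as time-updated: ATD until the procedure, then radioiodine or thyroidectomy. Estimate the weights from covariates measured at each treatment decision. Measure baseline fT4 in the same window around diagnosis in all arms. Use pre-procedure ATD time and time since diagnosis only in a propensity model for radioiodine versus thyroidectomy.

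Deleting those two covariates from the three-arm model would cure the separation but leave the mortality bias, so it is not sufficient alone.

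No new data are needed. The cost is re-coding person-time, fitting time-varying weights, and restating the estimand. Patients assigned to radioiodine through the levothyroxine proxy have no recorded procedure date, so a rule is needed for when their exposure changes.

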### Confounding

Based on the literature and clinical experience, we identified a number of confounders affecting both the exposure and the outcomes of our study. The modelled outcomes will be adjusted for baseline data (sex, age, IMD quartiles, smoking status and comorbidities) and time-varying covariates (thyroid function, cumulative time on the medical treatment, time since diagnosis, levothyroxine replacement, pregnancy and diagnosis of cancer). Table 2 presents the details of how covariates are defined and handled. Figure 1 depicts the directed acyclic graphs representing the relationship between the covariates. We will explore the relationships between the potential confounders and both exposures and outcomes independently in order to establish their potential role in this particular dataset.

**Table 2 T2:** Definitions of study covariates

Variable	Definition
Aetiology of hyperthyroidism	Identified based on Read codes and categorised in (1) Graves’ disease, (2) toxic nodular goitre and (3) undefined. The undefined category will consist of unspecified diagnosis and missing aetiology data.
Age	Age at index date
Baseline fT4	The highest measurement between 3 months prior to diagnosis and the index date
BMI	Normal (or underweight) <25 kg/m^2^, overweight 25–30 kg/m^2^ and obese ≥30 kg/m^2^; additionally, BMI status will be deduced from the Read code
Cancer diagnosis	Switch-type binary variable assuming lifelong status of cancer comorbidity
Frequency of GP visits	Time-varying variable of number of GP visits in a unit of time
IMD	IMD will be stratified into quintiles.
Levothyroxine (LT4) replacement	Switch-type binary variable assuming lifelong LT4 administration following development of hypothyroidism in radioiodine and thyroidectomy treatment groups
Pregnancy	Time-varying binary variable recording pregnancy
Pretreatment ATD	Cumulative time on ATD between diagnosis and the index date
Sex	Binary variable
Smoking status	As recorded at the index date, last observation carried forward if not available at the index date
TSH	Serial TSH, log-transformed for the analysis
Time since diagnosis	Time-varying variable measuring cumulative time since diagnosis

ATD, antithyroid drug; BMI, body mass index; GP, general practitioner; IMD, Index of Multiple Deprivation; TSH, thyroid-stimulating hormone.

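### Baseline comorbidities are promised as an adjustment but appear in neither the propensity covariates nor the outcome-model covariates, so the secondary comparisons can stay confounded by prior cardiometabolic disease

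*Protocol article*

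**What the plan says.** All references are to the Protocol article.

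- **Confounding section.** The modelled outcomes are to be "adjusted for baseline data (sex, age, IMD quartiles, smoking status and comorbidities"), together with several time-varying covariates, among them a cancer diagnosis. In Table 2 the only comorbidity with a definition is cancer, as a lifelong switch-type indicator.
- **Cardiometabolic risks and mortality, propensity model.** "The model will be developed using the following covariates: age at the index date, sex, baseline serum fT4, aetiology of hyperthyroidism, smoking status, IMD", followed by "cumulative time on ATD between diagnosis and the index date, time since diagnosis and BMI status". That makes nine covariates.
- **Same section, selection.** "Variables related to treatment, as an outcome, at p<0.10 will be selected for inclusion in the multiple propensity weights". To find them, "we will conduct several regression analyses with the treatment as a dependent and each potential confounder as an independent variable".
- **Same section, balance.** After weighting, "pairwise balance in the distribution of all included variables between the three treatment groups will be tested". The criterion is: "The propensity weights will be considered balanced if there are no statistically significant (p<0.05) differences". Variables that fail are added to the outcome model as a doubly robust step.
- **Same section, division of labour.** Inverse propensity weighting is given the task of removing baseline confounding. The remaining adjustments are levothyroxine treatment, log TSH and frequency of GP visits, all measured after the index date.

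**The concern.** The outcomes here are MACE, type 2 diabetes, heart failure, ischaemic heart disease, stroke and TIA, and cardiovascular and all-cause death. Prior cardiovascular disease or diabetes plausibly influences both the choice among drugs, radioiodine and surgery and the risk of these events. The Population section does not exclude patients with such disease. The Introduction itself gives atrial fibrillation in 2%–20% of untreated patients and mentions heart failure and thromboembolism as complications, so cardiac disease at baseline is to be expected.

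One section promises adjustment for comorbidities. The section that specifies the analysis gives them no place, either in the weights or in the outcome model. The safeguards cannot repair this: an omitted variable is never tested for balance, so it never triggers the doubly robust step. At stake is whether differences in cardiovascular events and death between treatments can be read causally, as that section intends.

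The two p-value rules are a separate weakness. The selection rule looks only at association with treatment, so it can keep a predictor of treatment that has no bearing on outcome and drop a strong prognostic factor. The balance rule measures precision as much as imbalance.

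**Working it through.** The article states no figure on this point, so there is nothing to reproduce. It gives no arm sizes, event rates or comorbidity prevalences; all numerical inputs in steps 2 to 4 are assumptions.

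**Step 1. Where does prior disease enter?**

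| Place | Covariates | Prior cardiometabolic disease? |
|---|---|---|
| Confounding, text | sex, age, IMD, smoking, comorbidities; time-varying items including cancer | Promised, not itemised |
| Table 2 | includes cancer, aetiology, baseline fT4, BMI | Not defined |
| Propensity model | age, sex, fT4, aetiology, smoking, IMD, ATD time, time since diagnosis, BMI status | Absent |
| Outcome-model adjustments | levothyroxine, log TSH, GP visits | Absent |
| Balance check and doubly robust step | variables included in the weights | Absent |

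Only the first row contains it, and no later row carries it out.

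**Step 2. Possible size of the bias.** Suppose a binary comorbidity multiplies risk by RR and has prevalence p1 in one arm and p0 in another after weighting on the listed covariates. The spurious ratio is (1 + p1(RR − 1)) / (1 + p0(RR − 1)). Take p0 = 0.10:

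| p1 | RR = 2 | RR = 3 |
|---|---|---|
| 0.13 | 1.13/1.10 = 1.03 | 1.26/1.20 = 1.05 |
| 0.15 | 1.15/1.10 = 1.05 | 1.30/1.20 = 1.08 |
| 0.20 | 1.20/1.10 = 1.09 | 1.40/1.20 = 1.17 |

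The prevalences are those left after weighting. Age, smoking and BMI will absorb part of any crude imbalance.

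**Step 3. The p-value rules and arm size.** The standardised difference that just reaches significance is z × √(1/n1 + 1/n2), with z = 1.96 for p<0.05 and 1.645 for p<0.10:

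| n1, n2 | p<0.05 | p<0.10 |
|---|---|---|
| 200, 2000 | 0.145 | 0.122 |
| 500, 5000 | 0.092 | 0.077 |
| 1000, 5000 | 0.068 | 0.057 |
| 3000, 9000 | 0.041 | 0.035 |

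Weighting lowers the effective sample size, so the limits after weighting would be somewhat larger.

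Next, take a true imbalance of 13% against 10%, a standardised difference of 0.03/√((0.13×0.87 + 0.10×0.90)/2) = 0.09. The chance of detecting it is Φ((0.03 − z·SE0)/SE1), where SE0 uses the pooled proportion and SE1 the separate ones. With arms of 200 and 2000, SE0 = 0.0225 and SE1 = 0.0247, giving 39% at p<0.10 and 28% at p<0.05. The same calculation gives:

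- 500 and 5000: 66% and 55%
- 1000 and 5000: 86% and 79%
- 3000 and 9000: over 99% for both

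**Step 4. False flags.** With perfect balance, nine independent tests at 0.05 give at least one false flag with probability 1 − 0.95^9 = 37%. Nine covariates by three pairs give 1 − 0.95^27 = 75%. Independence is a simplification.

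**The case against.** The best defence is that the Confounding section does promise outcome adjustment for comorbidities, and that the wording on testing each potential confounder could reach beyond the nine listed. The directed acyclic graph is not visible to this review, and an article condenses a fuller plan. This stands to the extent that the defect is a contradiction. A reader might infer that confounding by prior disease certainly remains after weighting; the document does not settle that. It does not remove the point, because the covariate list is stated and conflicts with the promise. Even on the wider reading, comorbidities would enter only if they passed the p<0.10 screen.

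Four other stronger readings are tempting and should not be drawn:

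- *The p-value rules cause the confounding by prior disease.* They do not; the omission does.
- *The primary weight model lacks aetiology and baseline fT4.* Table 2 defines both as study covariates, and thyroid function is listed as a time-varying adjustment. At most the sentence and the table differ.
- *Cancer is left unadjusted.* It is absent from the weights but is listed as a time-varying adjustment with lifelong status, which would carry a pre-index diagnosis.
- *The surgery arm is small, so the tests will miss real imbalance.* No arm sizes are given, and the article describes a large sample. In the three larger scenarios of step 3, the p<0.05 rule is stricter than a limit of 0.10.

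It is also fair that a flagged variable is merely added to the outcome model, which is a harmless consequence, and that the plan will explore how confounders relate to outcomes. The stated inclusion rule, however, does not use that exploration.

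**Conclusion.** The point holds as a contradiction with a practical consequence. Followed as written, the Cardiometabolic risks and mortality section leaves prior cardiometabolic disease out of both the weights and the outcome models, and no check in the plan would reveal it. The comparisons of MACE, other cardiometabolic outcomes and mortality can therefore remain confounded. These are secondary outcomes; the conclusion does not extend to the primary weight analysis.

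The size is unknown. The range of about 1.03 to 1.17 assumes a comorbidity that doubles or triples risk, with prevalence 10% in one arm and 13% to 20% in another after weighting.

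The screening and balance rules are a separate and lesser fault. Depending on arm size, they can pass a real imbalance or flag a trivial one. How far this matters here cannot be judged without the arm sizes.

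**What to change.** **Main change.** Reconcile the Confounding section, Table 2 and the propensity covariate list. Define pre-index cardiometabolic comorbidities from the linked CPRD and HES data (for example cardiovascular disease, atrial fibrillation, heart failure, hypertension and diabetes), add them to Table 2, and force them into the propensity model.

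**Lesser change.** Fix the confounder set in advance from prior knowledge and the directed acyclic graph, with no p-value screening. Replace the p<0.05 balance rule by weighted standardised differences, for example a maximum pairwise absolute value below 0.10, and add any variable above the limit to the outcome model. The 0.10 limit is a convention, not a figure from the article.

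**Cost.** Extra code lists, revised wording and slightly more variable weights. No new data source is needed.
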